### Statistical analysis

Statistical methods to assess differences between groups will be ANOVA and ANCOVA analyses and Mann Whitney U tests. Between group comparisons will be made for primary and secondary outcome measures. Effect sizes (D) will be calculated to determine the practical significance of these differences. D-values greater than 0.5 indicate a moderate and values greater than 0.8 will indicate a large practical significance [60]. Potential confounders, such as age, gender and score on the ADHD questionnaire, will be included in an ANCOVA.

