### Patient population

All children between the ages of 7 and 12 years admitted at the rehabilitation centers and private practices for occupational and physical therapy for training of their motor abilities in the participating centers will be considered for inclusion. They will be offered participation in the study if they fulfill all of the following criteria (according to the DSM-V criteria for DCD [1]):Motor ability substantially below expected level given the chronological age of the child (criterion A). The Movement Assessment Battery for Children (m-ABC - 2^nd^ edition) will be used to assess the motor abilities [30]. A total percentile score ≤ 16^th^ or a component score ≤ 5^th^ is needed for inclusion.Motor impairment significantly interferes with daily life and/or academic achievement (criterion B). Only children that are referred to the centers for training of their motor abilities are included in this study. Referral for training of motor abilities is a strong indication that the motor impairment either causes problems in daily life, or with academic achievement. In addition, as recommended, the DCD Questionnaire (DCDQ) will be used to assess whether the motor impairment has an impact on the daily life or academic achievement of the child (Dutch translation DCD-Q [31]).Onset of symptoms is in the early developmental period (criterion C) as evidenced by their referral to a centre for training of their motor abilities between the ages of 7–12 years.No medical condition that could cause the motor impairment is known and IQ ≥ 70 (criterion D). This will be checked by using a health questionnaire that will be filled in by the parents/caregivers of the participating children. If parents do not report learning difficulties and the child attends a regular primary school, an IQ ≥ 70 is assumed. When attending special education, parents are asked to fill in the latest IQ score of their child.

In addition to the above mentioned criteria, attentional problems are assessed by using the attention deficit hyperactivity disorder (ADHD) questionnaire [32]. Parents/caregivers of participating children will be asked to fill in this questionnaire to be able to check in the off-line analysis if attentional problems are a confounder.

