### Sample size

The smallest detectable difference (SDD 95 %), regarded as clinically relevant of the m-ABC-2 as reported in the manual is two standard scores [30]. Using the SDD 95 % as the cut off, it will be established how many of the children improved their total standard score on the m-ABC-2 in the two groups. The number of participants is based on this SDD 95 %, with a statistical power of 80 % and an α = 5 % (two-tailed). Because the main question is whether the MI training group has a greater improvement of motor abilities than the CO-OP training group after the intervention, the sample size calculation is based on the difference between the MI and CO-OP training on the m-ABC-2 change score (before and after training). Power calculations yielded a required sample size of 58 participants, 29 participants in each group.

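### No single test is designated for the m-ABC-2 comparison, and the baseline m-ABC-2 is not among the covariates named for the ANCOVA

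*Protocol article*

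**What the plan says.** All places are in the Methods/Design part of the protocol article.

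- **Statistical analysis, tests.** "Statistical methods to assess differences between groups will be ANOVA and ANCOVA analyses and Mann Whitney U tests". The next sentence applies these methods to primary and secondary outcomes together. No test is tied to the m-ABC-2.
- **Statistical analysis, covariates.** "Potential confounders, such as age, gender and score on the ADHD questionnaire, will be included in an ANCOVA".
- **Patient population.** The ADHD questionnaire is collected "to be able to check in the off-line analysis if attentional problems are a confounder".
- **Primary outcome measure.** The outcome is the m-ABC-2 score. The section does not say whether the post-treatment score or the change is compared.
- **Sample size.** "the sample size calculation is based on the difference between the MI and CO-OP training on the m-ABC-2 change score". The same section also plans to count, per group, the children whose total standard score improves by the smallest detectable difference (SDD).
- **Outcome measures.** A blinded assessor tests every child before and after treatment, so a baseline m-ABC-2 exists for all.

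**The concern.** There are two separate issues.

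**Error control.** The two-tailed 5% level in the Sample size section holds for one test fixed in advance. Here three methods are listed, the covariate list is open-ended, and the form of the outcome is explicit only where the trial is sized. On this text alone, several p-values could each be presented as the primary result.

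**Precision.** The baseline value of an outcome is usually its best single predictor. Age, gender and ADHD score are named as covariates and the baseline m-ABC-2 is not. Subtracting baseline gives it a fixed weight of 1, whereas ANCOVA estimates the weight from the data. When the true slope is below 1, subtraction adds noise and over-corrects chance baseline imbalance.

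**Working it through.** **1. The plan's own sample size.** Stated inputs are 80% power, two-sided alpha 0.05, and an SDD for which the article says "regarded as clinically relevant of the m-ABC-2 as reported in the manual is two standard scores". The stated result is 29 per arm. No SD of change, pre-post correlation or dropout rate is given, so 29 can only be back-solved. I read 2 points as the between-group difference in change.

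- Normal approximation: n per arm = 2(1.960 + 0.842)² SD² / 2² = 3.92 SD². Setting n = 29 gives SD = 2.72 (d = 2/2.72 = 0.74).
- Exact t-test: n = 29 gives d = 0.749, so SD = 2/0.749 = 2.67.
- Sensitivity (t-test): SD 2.5 needs 26 per arm and SD 3.0 needs 37.

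The figure of 29 is plausible but cannot be verified. Below I take the change-score analysis to have exactly 80% power at 29 per arm (d = 0.749).

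**2. Power with baseline as covariate, equal pre and post SDs.** Let the common variance be s² and the correlation r (assumed).

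- Change score: variance 2s²(1 − r).
- Baseline-adjusted ANCOVA: residual variance s²(1 − r²).
- Ratio: (1 − r²) / [2(1 − r)] = (1 + r)/2.

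| r | ratio | effective d = 0.749/√ratio | power at 29 per arm | n per arm for 80% |
|---|---|---|---|---|
| 0.5 | 0.75 | 0.864 | 89.9% | 22 |
| 0.6 | 0.80 | 0.837 | 87.9% | 24 |
| 0.7 | 0.85 | 0.812 | 86.0% | 25 |

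**3. The same with restricted baseline variance.** Entry requires a total score at or below the 16th percentile or a component at or below the 5th. As an extreme illustration, assume normal scores cut hard at the 16th percentile (z = −0.994) on the baseline measurement itself, with r the correlation before selection. With λ = φ(z)/0.16 = 1.521, the baseline variance falls to v = 1 − zλ − λ² = 0.20 of its unselected value.

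- Change-score variance: (1 − r²) + v(1 − r)².
- ANCOVA residual variance: 1 − r².
- Ratio: (1 + r) / [(1 + r) + v(1 − r)].
- r = 0.5: 1.5/1.6 = 0.94, d = 0.773, power 82%.
- r = 0.7: 1.7/1.76 = 0.97, d = 0.762, power 81%.

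Entry by the component route would soften the truncation, so the truth may lie between steps 2 and 3.

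**4. Cost of an undesignated test.** I simulated trials with no effect: 29 per arm, 8,000 trials per value of r, equal SDs, other covariates unrelated to outcome. Each test alone rejects about 5% of the time. Rejection rates when the smallest p-value is always reported:

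| choice allowed | type I error |
|---|---|
| change score: ANOVA, ANCOVA (age, gender, ADHD), Mann-Whitney | 6.5-7% |
| as above, with baseline-adjusted ANCOVA replacing the named-covariate ANCOVA | 7-8% |
| unadjusted post-score comparisons also allowed | 10-12%, depending on the set |

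**5. Outcome form and power.** With equal SDs, the variance of the unadjusted post score relative to the change score is 1/[2(1 − r)]. At r = 0.5 the ratio is 1.00 and power stays at 80%. At r = 0.7 it is 1.67, d = 0.749/√1.67 = 0.58, and power is 58%.

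**The case against.** A good deal can be said for the plan.

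- A reader might infer that baseline is left out of the model. The article does not say so. Its covariates are given as examples, ANCOVA is also listed on its own in a pre-post design, and baseline already enters through the change score. This objection stands: baseline is unnamed, not excluded.
- A reader might infer that power is wasted. A change-score comparison in a randomised trial is unbiased and, on the plan's own terms, has the stated 80% power. The effect size of 0.75 is back-solved, and step 3 shows the gain may be one or two points. This stands: the gain is an efficiency argument of uncertain size.
- A reader might infer that all covariates are picked after seeing the data. The Statistical analysis section says they will be included, without condition. The off-line check in Patient population concerns attentional problems only. This stands, although the open list still leaves the final set unfixed.
- The three tests need not compete for the m-ABC-2. Mann-Whitney suits the 5-point questionnaire items and the Enjoyment Scale. That is a reasonable guess, but the text applies one list to primary and secondary outcomes and gives no assignment.
- Adjusting an age-normed score for age is close to harmless. Agreed.
- The inflation figures assume an analyst who always reports the smallest p-value, and the 10-12% needs post-score tests although the sizing section frames the question as change. They are ceilings for each menu, not forecasts.
- An analysis plan not shown may settle all this. It may. The point rests on what the article does fix: a menu of tests and an open list of covariates.

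**Conclusion.** The point holds in a limited form. The article does not designate a test for the primary comparison and does not name the baseline m-ABC-2 among its covariates. It is not evidence that the trial will ignore baseline, nor that the change-score analysis is wrong.

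The error-control side is moderate: about 6.5-7% instead of 5% for free choice among the listed tests on the change score, and about 10-12% if the outcome form is free too. It does not depend on an SD, and hardly on the correlation over the range simulated.

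The precision side depends on assumptions. The gain is about 6 to 10 points of power with equal SDs and a correlation of 0.5 to 0.7, and about 1 to 2 points if the entry cut-off strongly truncates baseline. Neither the SD nor the correlation is in the document.

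This is a free or cheap improvement that should be made before outcome data are seen by group.

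**What to change.** In the Statistical analysis section, name one primary analysis: an ANCOVA of the post-treatment m-ABC-2 total standard score on arm, with the baseline m-ABC-2 total standard score and a closed list of further covariates. The three already named could form that list. Include them whatever imbalance or association is observed, so that the attentional-problems check no longer decides model content. State the outcome form in the Primary outcome section to match. Make the change-score, Mann-Whitney and SDD-responder comparisons supportive, and say which secondary outcomes Mann-Whitney is meant for.

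The cost is wording and one or two degrees of freedom. With arm, baseline, age, gender and ADHD score fitted to 58 children, 58 − 6 = 52 residual degrees of freedom remain, one fewer than without baseline. No new data are needed, and a sample sized on the change score stays sufficient apart from that degree of freedom.

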### Study organization

The study is organized and coordinated by the Radboud University in Nijmegen, the Netherlands. Collaborating institutions are 2 rehabilitation centers in the Netherlands and 17 private practices for occupational and physical therapy across the Netherlands.

## Discussion

MI training is already described as a possible treatment for children with DCD [9], but it is not recommended yet because there is only one study available [22]. The study of Wilson et al. [22] showed training effects comparable to conventional physical therapy. However, 39 % of the sample had a test score within the low normal range on the m-ABC. Therefore, conclusions about MI training for DCD should be interpreted with care. It is important to study whether MI training is also effective in a population with scores in the clinical range of the m-ABC-2 that meet the DSM-V diagnostic criteria for DCD.

Moreover, the multicenter character of the study will increase the generalizability of study results across different rehabilitation centers and private practices for occupational and physical therapy. The present study will also provide an opportunity to evaluate the feasibility of MI training both from the therapists’ and children’s point of view. As a result, the present study will also help to gather information needed to implement MI training on a larger scale. This study will increase our knowledge about the efficacy of both the MI training and CO-OP training, and therefore will help to make treatment protocols for children with DCD more evidence-based, from which both children with DCD and therapists will benefit.

## Abbreviations

ADHD: attention deficit hyperactivity disorder
ANCOVA: analysis of co-variance
ANOVA: analysis of variance
CO-OP: cognitive orientation to daily occupational performance
DCD: developmental coordination disorder
DCDQ: developmental coordination disorder questionnaire
DSM: diagnostic and statistical manual of mental disorders
EACD: European Academy for Childhood Disability
IMD: internal modeling deficit
m-ABC: movement assessment battery for children
MI: motor imagery
NTT: neuromotor task training
SDD: smallest detectable difference
SOS: systematische opsporing schrijfproblemen
